Thus, we hypothesize that KDs and FDs are superior to the SD with respect to new lesions on cranial T2-weighted MRI after 18 months compared to baseline. We further hypothesize differential effects of our interventions in men and women, because of sex-specific metabolic differences (e.g. fat and carbohydrate metabolism). We further expect larger treatment effects in patients without MS medication.

Secondary endpoints are safety aspects of the dietary interventions, brain volume, annualized relapse rate, disability progression, changes in gut microbiome, metabolomics of stool and blood, immunological effects, cognition, fatigue, depression, muscle strength, walking endurance and quality of life.

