### Power calculation

Based on the results of other MS studies in our research center in comparable patient cohorts, an average of three new T2 lesions after 18 months is expected in the SD group. Sample size was calculated with the Wilcoxon (Mann–Whitney) rank-sum test and the significance level was adjusted (Bonferroni) for the two comparisons (KD vs. SD and FD vs. SD). With a sample size of 33 patients per group and a two-sided significance level of 0.025, there is a power of 80% to detect a probability of 0.72 that an observation from group 1 is smaller than that from group 2. This corresponds to a standardized effect size of 0.83 and an expected mean difference in the number of new T2 lesions in each of the intervention groups of 0.5 compared to the SD group after 18 months (Query Advisor 7.0). We expect a dropout rate of approximately 10% and therefore plan to enroll 37 patients per group, 111 patients in total.

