### Data analysis

Confirmatory analysis will be conducted based on the intention-to-treat (ITT) population. The aim is to show that KDs and FDs are superior to the SD, meaning that the number of new T2 lesions after 18 months of dietary intervention adjusted for the baseline value is lower in the KD and FD groups than in the SD group. Although the sample size calculation was conservatively based on the Mann–Whitney *U* test, the final analysis of the primary endpoint will be based on non-parametric analysis of covariance (ANCOVA) on ranks with the treatment group as a fixed factor and adjustment for the baseline number of T2 lesions. The resulting coefficients will be reported with 95% confidence intervals and their corresponding *p*-values compared to a two-sided Bonferroni-adjusted significance level of 0.025 [48].

We do not plan any interim analyses. In the case of more than 5% missing for the primary endpoint, we plan to replace missing values in the outcome parameter using multiple imputation [49] under the missing at random assumption in addition to the complete case analyses.

As a sensitivity analysis, the primary endpoint will be analyzed in the per-protocol population. This population includes all randomized patients who meet the study eligibility criteria and fulfill all compliance criteria throughout the study.

We intend to perform two subgroup analyses, men vs. women and MS medication vs. no MS medication, by adding another main effect for sex or medication, respectively, as well as an interaction term. These subgroup analyses will be analyzed in an exploratory manner to generate possible hypotheses for follow-up studies without adjustment for multiple comparisons. For these, *p*-values may not be interpreted as confirmative.

Safety analysis will include calculation of frequencies and rates of adverse and serious adverse events within 18 months of the interventions.

Secondary endpoints will be analyzed in an explorative manner and descriptives will be given using the mean and standard deviation for sufficiently normal distributed metric variables, the median with limits of the interquartile range (IQR: 25th and 75th percentiles) for skewed metric or ordinal data, as well as absolute and relative frequencies for count data.

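### The only effect measure fixed for the primary endpoint is a rank coefficient with a 95% interval, and the subgroup interactions inherit that scale, so neither can be read in lesions

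*Protocol article*

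**What the plan says.** All places are in the protocol article.

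- **Aim (Data analysis).** It is framed in lesions, with the standard diet as the comparator: "the number of new T2 lesions after 18 months of dietary intervention adjusted for the baseline value is lower in the KD and FD groups".
- **Planning (Power calculation).** "an average of three new T2 lesions after 18 months is expected in the SD group", and the expected mean difference for each diet is 0.5 lesions. The calculation itself uses the rank-sum test with a probability of 0.72.
- **Primary analysis (Data analysis).** The analysis "will be based on non-parametric analysis of covariance (ANCOVA) on ranks with the treatment group as a fixed factor", adjusted for the baseline T2 lesion number. "The resulting coefficients will be reported with 95% confidence intervals", and the p-values are judged at a two-sided 0.025.
- **Subgroups (Data analysis).** Sex and medication are examined "by adding another main effect for sex or medication, respectively, as well as an interaction term". The text adds: "These subgroup analyses will be analyzed in an exploratory manner to generate possible hypotheses for follow-up studies". It also says that their p-values are not confirmatory.
- **Expected direction (Introduction).** "We further expect larger treatment effects in patients without MS medication". No scale is named for that effect.

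**The concern.** A rank-ANCOVA coefficient is a difference in adjusted mean rank. Its size depends on the number of patients ranked and on ties, and nothing in the output turns it into lesions. A reader who wants to know how many lesions a diet prevents, or how the result compares with the planned 0.5, gets no answer from the measure that the plan fixes. A 95% interval can also exclude zero where the test at 0.025 does not reject.

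The interaction raises a related problem. If medicated patients have far fewer lesions, they crowd the tied low ranks. A diet with the same proportional effect in both groups then moves them by fewer ranks. The subgroup analysis is meant to suggest hypotheses for later trials, and a hypothesis about effect modification needs a stated scale.

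**Working it through.** **1. The plan's own figures.** Noether's formula for the rank-sum test gives n = (z₀.₉₈₇₅ + z₀.₈₀)² / [6(0.72 − 0.5)²] = (2.241 + 0.842)² / (6 × 0.0484) = 32.7, so 33 per group. Dropout of 10% gives 33/0.9 = 36.7, so 37. The standardized effect is √2 × z(0.72) = 0.824 (stated 0.83). The sample size reproduces and this point does not change it.

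**2. What the rank coefficient measures.** Ignore the covariate and let the third arm share the distribution of one of the other two. The mean-rank difference is then N × (P − 0.5), where P is the probability used in the power calculation. At P = 0.72 this is 99 × 0.22 = 21.8 ranks with 99 patients and 111 × 0.22 = 24.4 ranks with 111. The separation is the same but the coefficient differs, and neither number says anything about 0.5 lesions.

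**3. Interval against test.** A 95% interval uses 1.960 standard errors, and a 0.025 test needs 2.241. The matching 97.5% interval is 2.241/1.960 = 1.14 times as wide. Any p-value between 0.025 and 0.05 comes with a 95% interval that excludes zero although the test fails.

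**4. Interaction on ranks, common rate ratio.** Lesion rates by medication, dispersion and the medicated share are not in the article. They are assumptions, shown over a range. Base case: 99 patients, overall SD mean of 3, 60% medicated, both diets at rate ratio 0.4 in both medication groups, negative binomial counts (variance μ + μ²/k) or Poisson. Ranks are regressed on treatment, medication and their interaction, tested at 0.05.

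| Lesion rate, medicated relative to unmedicated | Rejection |
|---|---|
| 1/2 | about 5–7% |
| 1/4 | about 6–11% |
| 1/10 | about 10–28% (upper end: Poisson) |

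At 1/4, mean rank effects (unmedicated vs medicated) are −16.0 vs −12.9 (k = 1), −19.7 vs −15.1 (k = 2) and −26.6 vs −17.6 (Poisson).

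The planned 0.5 fewer lesions out of 3 is a rate ratio of 2.5/3 = 0.83. There, rejection stays between about 4% and 7% in every scenario.

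**5. The same question with baseline adjustment.** This simulation used 3 × 33 patients, 2,000 runs per scenario and the baseline rank in the model.

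- *No diet effect:* rejection 4.1–5.1%, so the level holds.
- *Common ratio (0.7 to 0.35), SD means 4.5 and 1.5:* rejection 4.4–8.0%. Signals towards a larger effect off medication occur in 2.7–8.2% (nominal 2.5%).
- *Common ratio 0.35, means 5.4 vs 0.6, or 9 vs 0.5 with 70% medicated:* rejection 12–13%.
- *Similar groups (3.5 vs 2.5):* 3.3–3.5% in that direction (nominal 2.5%).
- *Constant absolute reduction of 1 lesion, means 4.5 and 1.5:* −4.5 ranks unmedicated vs −14.7 medicated, rejection 13.3%. With 1.2 lesions and less dispersion it is 22%. With 0.5 lesions it is 6.0–6.5%. The signal now favours the medicated.

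**The case against.** - **The article is condensed.** It does not rule out lesion summaries, and a fuller plan may contain them. This stands. A reader might infer that no effect in lesions will be reported, but the text supports only that none is specified. What remains is that the article does fix an effect measure, and that measure does not express its own aim.
- **The planning is itself rank-based.** Dividing the coefficient by N approximately recovers the probability to be compared with 0.72. This stands too. Only the 0.5-lesion figure is out of reach.
- **The rank interaction does not simply manufacture the medication effect that the Introduction expects.** That stronger reading is tempting but unsupported. With SD means of 4.5 and 1.5, a common ratio of 0.4 removes 4.5 × 0.6 = 2.7 lesions off medication and 1.5 × 0.6 = 0.9 on it. In lesions the effect really is larger off medication, so the signal is spurious only on the ratio scale. Under a constant absolute reduction it runs the other way.
- **The large rejection figures need a strong diet effect and a wide rate gap together.** Correct. A ratio of 0.4 is not arbitrary, though: it corresponds to a probability of 0.67–0.81 depending on dispersion, which brackets the planned 0.72.
- **The negative binomial test is not clearly better calibrated in moderate scenarios.** It rejected in 3.0–8.6% with known dispersion (Monte Carlo error about 1 point), against 4.4–8.0% for ranks. True. The reason to change is a nameable scale, not mainly error control.
- **The subgroups are declared exploratory.** This limits the harm and protects the confirmatory conclusion.

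**Conclusion.** The point holds in a limited form. The effect measure fixed for the primary endpoint cannot be read in lesions, and its 95% interval does not match the 0.025 test. Neither statement rests on simulation.

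The interaction, read as an extension of the rank model, matches neither a ratio nor an absolute lesion effect. If the diets work and lesion rates differ strongly by medication, it can produce or mask an apparent medication interaction. The size runs from negligible (rate ratio 0.83, similar groups, or no diet effect) to 10–28% rejection at a tenfold rate gap with ratio 0.4, all under assumed inputs.

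The rank test as the confirmatory test, the sample size and the significance level are unaffected.

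**What to change.** 1. Keep the rank ANCOVA as the confirmatory test at 0.025, and state that it alone decides superiority.
2. Add a negative binomial model (log link, same covariates, robust standard errors). Report the rate ratio for each diet against SD and adjusted mean lesion counts per arm, with 97.5% intervals. If the rank coefficient is still shown, give it the same interval level.
3. Estimate the exploratory sex and medication interactions in that model instead of on ranks, as ratios of rate ratios together with absolute lesion differences by stratum. The reader can then see whether an apparent interaction depends on the scale.

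The cost is some analysis-plan wording and one extra model. The downside is a distributional assumption that touches only the estimate. It is softened by the robust errors and by leaving the test unchanged. The model-based interval may occasionally disagree with the rank test, which is why step 1 should say which one decides.

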#### Complete list of exclusion criteria

Start or change of immunomodulatory therapy < 6 months before or during the studyRelapse or cortisone treatment within 30 days before study entryClinically relevant metabolic, progressive or malignant diseasesIntake of > 1 g/day omega-3 fatty acid supplementsSignificant cognitive-cooperative impairmentInsulin-dependent diabetes mellitus (type I)Participation in another interventional studyWeight loss diet or loss of more than 5 kg within 2 months before study entryInsufficient mental ability for cooperationEating disordersKidney stonesTherapy with oral anticoagulantsPregnancy and breastfeedingSuspected lack of complianceSmokers (> 5 cigarettes per day)Known alcohol and drug abuseInability to give informed consent or apply to the study protocolContraindications for MRI such as metallic implants, cardiac pacemakers and claustrophobia

Retention of patients is promoted by close and frequent contact with their nutritional counselor and study physician via telephone, email and study visits. In case of relevant issues, visits outside the study schedule are offered.

Discontinuation criteria are withdrawal of consent, subsequent occurrence of an exclusion criterion (e.g. change of immunomodulatory therapy), lack of compliance and medical reasons for stopping the intervention.

For all three groups, compliance is defined as attending at least 8 of 10 group sessions and each of six study visits. Food records measure compliance to the prescribed intervention. In the KD group, the majority of blood ketone measurements should be ≥ 0.5 mmol/L. For the FD group, there are regular additional meetings during each of the three fasting periods. These meetings have to be attended, enabling the physician and the counselor to evaluate compliance.

We offer patients who meet a discontinuation criterion to attend the remaining study visits for follow-up outside the study protocol. We assess all outcomes except for exploratory blood parameters (autophagy, oxidative stress) in these patients.

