### Dietary interventions

Nutritional counseling for all three interventions takes place in small groups within 10 sessions over 18 months (five sessions in months 1–3, five sessions in months 4–18). The group setting facilitates exchange between patients, management of dietary challenges, monitoring of compliance and recording of adverse events. Between the group sessions, patients have the possibility to contact their nutritional counselor via email or telephone at any time.

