*KD*. During nutritional counseling, patients are instructed to start by limiting carbohydrate intake to just 20 g/day for 4 weeks in order to establish ketosis. Then, patients increase their carbohydrate intake by 5 g each week until they reach their individual maximum (approximately 40 g) to maintain stable ketosis. All carbohydrates relevant for elevating blood glucose are limited to 40–50 g/day. In addition, the glycemic index and glycemic load of carbohydrates have to be below 50 and 6, respectively. This ketogenic diet is equivalent to a traditional ketogenic diet, but with a liberalized macronutrient composition of 70–80% fats, 15–20% proteins and 5–10% carbohydrates (compared to a traditional ketogenic diet with 90% fat, 6% proteins and 4% carbohydrates). To aid in the adjustment and determine their individual carbohydrate intake limits, patients receive a hand-held ketone-meter to measure and record blood concentrations of ketone body β-hydroxybutyrate at regular intervals. Values should be between 0.5 and 3.0 mmol/L.*FD*. Patients in the FD group fast for 7 days every 6 months. During this intensive fasting episode, patients only consume vegetable juices and vegetable broth, yielding a daily calorie intake between 200 and 350 kcal. Tea and water is available *ad libitum* to ensure sufficient fluid intake. Two days before and 3 days after fasting, patients eat a low-calorie vegetarian diet for preparation and aftercare. The fasting is initialized by an intestinal clearing with laxatives (e.g. Glauber’s Salt by FX-Passage). Outside these intensive fasting episodes, patients intermittently fast for 14 h daily on 7 days of the week in order to maintain fasting effects. For compliance reasons, participants may take one “cheat day” per week at which they follow the fasting rules less strictly. During intermittent fasting, patients are counseled to eat a diet according to the recommendations of the DGE (equivalent to the SD group). Patients additionally attend group sessions every other day during fasting. A physician and a dietician with expertise on fasting monitor these sessions. During the first intensive fasting episode, these sessions are every other day. In the subsequent fasting episodes, the meetings are less frequent (three or four meetings).*SD*. Patients are counseled to adhere to a healthy, non-calorie-restricted diet according to the recommendations of the DGE. This diet is predominantly vegetarian with reduced consumption of meat, animal fats, eggs and egg products. Low-fat milk and dairy products are recommended to provide calcium. Dietary recommendations are designed to modify the omega-6 to omega-3 fatty acid ratio to 5:1.

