Beck Depression Inventory II	x				x		x
Fatigue Severity Scale	x				x		x
Physical examination	x				x		x
Multiple Sclerosis Functional Composite	x				x		x
Symbol Digit Modalities Test	x				x		x
Six-minute walk test	x				x		x
Expanded Disability Status Scale	x				x		x
Relapse query	x	x	x	x	x	x	x
AE/SAE query		x	x	x	x	x	x
MRI		x			x		x
Four-day food record		x			x		x
Nutritional counseling			x	*	*	*	*

*AE* adverse event, *MRI* magnetic resonance imaging, *SAE* serious adverse event

*There are 10 group sessions for nutritional counseling within 18 months. The fasting diet group has additional meetings during their 7-day-fasts at baseline and after 6 and 12 months

We will inform participants about any conspicuous findings and refer them to their general practitioner for further treatment. After completion of the study, participants have the possibility to be referred to appropriate outpatient nutritional counseling.

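### Recorded non-serious adverse event rates may be higher in the fasting arm partly through unequal ascertainment, and the safety analysis does not separate events by how they were found

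*Protocol article*

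**What the plan says.** The safety paragraph of the Data analysis section reads: "Safety analysis will include calculation of frequencies and rates of adverse and serious adverse events within 18 months of the interventions". It states no between-arm test and no breakdown by source of report.

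Events can be recorded by more than one route:

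- **Scheduled query.** Table 1 sets the AE/SAE query at visits 0 to 5, identically for every arm.
- **Group sessions.** Dietary interventions states: "The group setting facilitates exchange between patients, management of dietary challenges, monitoring of compliance and recording of adverse events". All arms have "10 sessions over 18 months (five sessions in months 1–3, five sessions in months 4–18").
- **General rule.** The Adverse events section has patients asked about tolerability and every event recorded, without restricting this to the scheduled query.

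Only FD has further meetings. The Table 1 footnote says: "The fasting diet group has additional meetings during their 7-day-fasts at baseline and after 6 and 12 months". Dietary interventions calls them group sessions and has a physician and a dietician monitor them. Their frequency is given in two sentences: "During the first intensive fasting episode, these sessions are every other day", and "In the subsequent fasting episodes, the meetings are less frequent (three or four meetings"). The text after the exclusion criteria makes attendance compulsory: "These meetings have to be attended, enabling the physician and the counselor to evaluate compliance".

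**The concern.** Safety is a named secondary endpoint, and the article's conclusion presents both KD and FD as potentially safe. The Adverse events section lists the same minor effects for KD and fasting (headache, hunger, fatigue, irritability, dizziness) and expects them to pass within days. A patient is likely to mention such complaints when asked the next day, and may not mention them at a visit months later.

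FD patients are seen by a physician every other day in their first fast and several times in each later one. KD and SD patients have no counterpart. Event rates from a three-arm trial will be read side by side whether or not a test is planned. If they are computed over all sources without a flag, a higher FD figure could reflect the diet, the closer observation, or both, and the data would not allow these to be told apart.

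**Working it through.** **1. Contacts common to all arms, months 0 to 18.** Group sessions: 5 + 5 = 10, which matches the stated total. Scheduled AE/SAE queries: six visits (0 to 5), but visit 0 is at month −1, before the intervention. Visits 1 to 5 (months 0, 3, 9, 15, 18) remain, so 5. Total: 10 + 5 = 15.

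**2. Extra FD meetings.** The article gives no total. Every other day over a 7-day fast is 4 meetings (days 1, 3, 5, 7). Each of the two later fasts has 3 or 4.

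- Low: 4 + 3 + 3 = 10
- High: 4 + 4 + 4 = 12

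The first-fast count depends on the reading. It is 3 if meetings start on day 2 (total 9 to 11). It is 6 if the 2 preparation and 3 aftercare days also count (total 12 to 14). The later fasts are described as having less frequent meetings, yet three or four meetings is what every other day over 7 days already gives. An adjacent sentence also states every other day for fasting in general. These statements should be reconciled.

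**3. Ratio of contact occasions, FD to KD or SD.**

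| First fast | Extra meetings | FD total | Ratio to 15 |
|---|---|---|---|
| 4 meetings | 10 to 12 | 25 to 27 | 1.67 to 1.80 |
| all readings | 9 to 14 | 24 to 29 | 1.60 to 1.93 |

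On the scheduled queries alone it is 5 against 5, ratio 1.0.

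**4. From contacts to recorded events.** This step needs assumptions the article does not supply. Assume equal true event rates in all arms, onsets uniform over 18 months (18 × 30.44 = 548 days), and an event recorded only if a contact follows within a recall window of *w* days. Place five sessions evenly over months 0.5 to 3 and five over months 4 to 17, with fasting meetings on days 1 to 7 and over six days from months 6 and 12.

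In KD and SD, the month 0 visit has no earlier time on diet to look back on, and one session falls on the month 3 visit, leaving 15 − 2 = 13 distinct contacts.

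- *w* = 3: the common contacts cover 13 × 3 = 39 days (39/548 = 0.071). Fasting meetings add 7 days in the first fast and 3 + 6 = 9 in each later fast, so 25. Ratio (39 + 25)/39 = 1.64.
- *w* = 7: the common contacts cover 13 × 7 = 91 days (91/548 = 0.166). Fasting meetings add 7 + 13 + 13 = 33. Ratio (91 + 33)/91 = 1.36.

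Longer windows make the covered periods overlap; the same model evaluated numerically gives:

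| Recall window (days) | FD/SD ratio of recorded events |
|---|---|
| 3 | 1.64 |
| 7 | 1.36 |
| 14 | 1.23 |
| 30 | 1.22 |
| 60 | 1.16 |
| 120 or more | 1.00 |

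Having three rather than four meetings in the later fasts does not change these ratios.

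**The case against.** **The link is inferred.** No sentence says that adverse events are recorded at the fasting meetings. Their stated purpose is to evaluate compliance, and the sentence on recording events sits in the paragraph on the ten common sessions. This stands as a limit on certainty. However, the article calls the fasting meetings group sessions, a physician attends, every event is to be recorded, and nothing excludes these meetings.

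**The excess may be real.** The extra meetings fall in the weeks when fasting side effects are most likely. This also stands, and it counts against removing fasting-week events from the main safety result.

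**Other contact is available to all arms.** Five common sessions fall in months 1 to 3, covering KD start-up, and every arm has telephone, email and unscheduled visits. This narrows the gap but does not remove it.

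**Source tabulation belongs in the case report form or the SAP.** Largely fair for the table. The source itself, if not captured when the event is reported, is hard to recover later.

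**Stronger readings.** A reader might infer that recorded events rise in proportion to contacts, by 1.7 to 1.8 times. The article does not support that: meetings two days apart largely cover the same days. A reader might also infer that the annualized relapse rate is affected. The article names adverse events, not relapses, for the group setting; relapse is queried at every visit in all arms; and nothing indicates that relapses are forgotten within days.

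**Conclusion.** The contact asymmetry follows from the text: about 15 occasions in KD and SD against 25 to 27 in FD over months 0 to 18, taking four meetings in the first fast. It creates a risk that recorded rates of non-serious events in FD are raised partly by ascertainment. It does not show that they are inflated, or that FD will look less safe. The recorded ratio under equal true rates lies between 1.0 and about 1.6 in the model above. The upper end needs recall as short as three days, and everything depends on events being recorded at the fasting meetings.

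Serious events are less likely to be affected. The primary endpoint, read from MRI by a blinded evaluator, and the sample size are untouched. The point is a cheap improvement to a secondary endpoint, not a flaw in the confirmatory analysis.

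**What to change.** Add a source field to each adverse event record: scheduled visit query, common group session, FD fasting meeting, or unscheduled contact. For events already recorded, assign the source from the reporting date where possible.

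In the analysis:

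1. Keep the all-source frequencies and rates by arm as planned.
2. Beside them, show rates by arm from the scheduled queries and group sessions common to all arms.
3. List separately the events found only at FD fasting meetings.
4. Leave serious events pooled over all sources.

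The common-contact rates should not replace the all-source rates, since they could hide genuine effects of fasting. An event already reported at a fasting meeting might otherwise have surfaced at the next common contact, so these rates may sit low for FD. Shown together, the two sets reveal how far the FD figure depends on the fasting meetings.

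The cost is one field and one table. The trial started in May 2017 and the article reflects protocol version 1.4 of September 2019, so source data for events already recorded will be incomplete. No visit, meeting or intervention changes.
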